### **3.4.2 Secondary endpoints**

- a. Number of readmissions
- b. Change in Self-Efficacy
- c. Health care utilization, measured as the number of re-admissions, and unscheduled outpatient visits due to unplanned visits to hospital and/or vårdcentral due to symptoms of COPD and CHF

### **3.5 Study design**

As outlined in section the overall study design is an experimental embedded research design (see also figure 1). In phase II of this project, we will run a randomized Controlled pilot study over a six months period. The intervention group will receive the PCC-PTS programme, the control group will receive usual care. This study is embedded in qualitative studies to obtain a better understanding of the mechanisms that affect the outcomes of the intervention.

[figure not shown]

Figure 2: Flowchart: RCT: Intervention and study design

### 3.6 Population and sample

Adult patients who have been hospitalized due to worsening CHF and/or COPD in one of Gothenburg's major hospitals (Sahlgrenska, Östra Sjukhuset) or to Skellefteå hospital.

#### 3.6.1 Enrolment

Patients will be enrolled to the program during their hospital stay, either from A&E or on the ward once their condition has stabilized sufficiently.

Specially trained RNs will screen and inform patients about the aims of the study, as well as its potential benefits for patients (see screening from in Appendix A). Patients will need a smartphone to participate in the study. Patients who do not own a smartphone will be provided with one for the duration of their participation in the programme.

### 3.6.2 Selection: control vs. intervention

Patients admitted to hospital for worsening COPD and/or CHF will be recruited by the research nurses employed in this project from Emergency or on the ward once their condition has stabilized sufficiently.

Patients will be screened against inclusion and exclusion criteria for eligibility to participate in the study. Written informed consent will be obtained. Patients will be randomized into either the control or the intervention arm 1:1. The control group will receive usual care. The intervention group will receive usual care plus a PCC nurse-led intervention. Randomization will be done through computer generated lists and stored in sealed envelopes.

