#### **Primary outcome measure: Self-efficacy**

- |            |                                                                                           |
|------------|-------------------------------------------------------------------------------------------|
| Improved:  | Increase in Self-efficacy > 5 units at 6 months and has not been re-admitted to hospital  |
| Worsened:  | Death or re-admitted to hospital within 6 months or a decrease in self-efficacy > 5 units |
| Unchanged: | Self-efficacy has neither improved or deteriorated                                        |

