### 3.6.3 Inclusion criteria

- History of confirmed diagnosis of COPD and /or CHF
- Admission to hospital for relapse /worsening symptoms of COPD and/or CHF
- Age:  $\geq 50$
- National registration within the Västra Götaland Region (VGR)
- Owning a phone and current subscription to a telephone service provider

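### Allocation concealment rests on sealed envelopes alone in a trial that cannot be masked; release by the coordinating centre after registration, from stratified blocked lists, would be stronger at little cost

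*Protocol*

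**What the plan says.** Protocol section 3.6.2 is the only place that describes allocation. It states "Patients will be randomized into either the control or the intervention arm 1:1" and then "Randomization will be done through computer generated lists and stored in sealed envelopes". It names no stratification factor, block scheme, envelope holder, opening procedure or central release.

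The same section says that eligible patients "will be recruited by the research nurses employed in this project from Emergency or on the ward once their condition has stabilized sufficiently". No criterion for sufficient stabilisation is given, and nobody else is named to judge it. On treatment it says "The intervention group will receive usual care plus a PCC nurse-led intervention"; controls receive usual care.

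Patients come from three hospitals (section 3.6: "in one of Gothenburg's major hospitals (Sahlgrenska, Östra Sjukhuset) or to Skellefteå hospital") and may have either disease or both (section 3.6.3: "History of confirmed diagnosis of COPD and /or CHF"). The primary outcome (section 3.4.1) counts a patient as improved on this condition: "Increase in Self-efficacy > 5 units at 6 months and has not been re-admitted to hospital". Death or re-admission counts as worsened. Self-efficacy is a patient self-assessment (section 3.8.1). Section 3.10 gives coordination of the study to GPCC.

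**The concern.** Four features together make concealment matter more than usual here.

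- Patients and nurses will know the arm from the start, because the intervention begins with a face-to-face meeting in hospital (section 3.7.2).
- Enrolment timing is flexible, so someone who knew or guessed the next assignment could wait, or approach a different patient.
- The team expects participants to benefit (section 3.12), which gives a motive, however well meant, to steer suitable patients towards the programme.
- Part of the primary outcome is self-reported, so placing more motivated patients in one arm would act on it directly. A larger sample would not average that out.

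A lesser matter is that hospital and diagnosis could plausibly relate to re-admission and to change in self-efficacy. With no stated stratification, their balance between arms is left to chance.

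**Working it through.** **The plan's own figure.** Section 3.6.5 gives 91 per group for 20% against 40% improved, with 80% power and alpha 0.05. The two-sided formula without continuity correction gives

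n0 = [1.96 × √(2 × 0.3 × 0.7) + 0.8416 × √(0.2 × 0.8 + 0.4 × 0.6)]² / 0.2² = (1.270 + 0.532)² / 0.04 ≈ 81.2, or 82 rounded up.

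With the continuity correction, n = (n0/4) × [1 + √(1 + 4/(n0 × 0.2))]² = 20.3 × (1 + 1.116)² ≈ 91. The stated figure is reproduced. Stratification and central release leave it, and the 110 per group to be enrolled, unchanged.

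**Concealment.** No arithmetic applies, because the documents give nothing from which to estimate how often an assignment might be foreseen. The check is of what the text secures. Section 3.6.2 lists screening, consent and randomisation in that order, and it has the lists sealed. It does not say that an assignment is released only after the patient is irrevocably registered, nor who has custody. The order of steps is described, but no mechanism enforces it.

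**Chance imbalance.** Hospital and diagnosis shares are not in the documents, so a share p is assumed. With 110 per arm, the standard deviation (SD) of the between-arm difference in share is √(2p(1−p)/110).

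| Assumed share p | SD of difference | Chance of a difference of 10 points or more (normal approximation) |
|---|---|---|
| 50% | √(0.50/110) = 6.7 points | z = 10/6.7 ≈ 1.48, so 13.8% |
| 30% | √(0.42/110) = 6.2 points | z = 10/6.2 ≈ 1.62, so 10.6% |

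Exact hypergeometric calculation gives 13.8% and 10.5%. It also gives 6% at a 20% share and 1% at a 10% share.

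**Effect on the result.** The shift in the treatment difference is the imbalance times the gap in improvement rate between strata. For a 10-point imbalance and assumed gaps of 10, 20 and 30 points, the shift is 0.10 × 0.10 = 1 point, 0.10 × 0.20 = 2 points and 0.10 × 0.30 = 3 points. The design effect is 20 points.

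**Against sampling error.** The standard error of the treatment difference at 110 per arm is √[(0.2 × 0.8 + 0.4 × 0.6)/110] = √(0.40/110) = 6.0 points. At a 50% share and a 20-point gap, the SD of the shift is 6.7 × 0.20 = 1.3 points. As a share of variance this is (1.3/6.0)² ≈ 5%.

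**Number of strata.** Three hospitals by three diagnosis groups make 9 strata, on average 220/9 ≈ 24 patients each.

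**The case against.** The other side has a good case, and much of it stands.

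- A reader might infer that the lists are simple and unblocked. The Protocol does not say so. It speaks of lists in the plural, which would fit one list per hospital or blocked lists.
- A reader might infer that the recruiting nurses hold or open the envelopes. No text says this, and custody at the coordinating centre is not excluded.
- If the lists were unblocked, past assignments would reveal nothing about the next one. Foresight would then need access to the envelopes themselves. Permuted blocks in small strata make guessing easier in an unmasked trial.
- A reader might infer that chance imbalance biases the comparison. It does not: its expectation is zero and the standard error already includes it. A shift of 2 points is a tail event under assumed inputs. COPD and CHF are recorded at baseline (section 3.8), and section 3.9 plans logistic regression on descriptive variables, so adjustment remains possible.
- Unstratified 1:1 allocation of 220 patients, in what section 3.5 calls a pilot, is an acceptable design. Strata and block settings may be in a separate randomisation plan.

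What does not fall is the concealment point. The Protocol fixes envelopes as the method and adds no safeguard beyond sealing, in a setting where foreknowledge would matter. That has to be settled before the first patient is enrolled; an analysis plan cannot restore it afterwards.

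**Conclusion.** The point holds as an inexpensive improvement, mainly to concealment. It does not show that the stated method is wrong or that selection will occur. Its main support is the combination of an unmaskable comparison, discretionary timing of recruitment and a partly self-reported primary outcome, with sealing as the only stated protection. That the trial is open is implied by its design rather than stated. The size of any selection bias cannot be derived from the documents.

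Stratification is secondary: a modest gain in precision and credibility. On the illustrative assumptions of a 50% share and a 20-point gap, the variance at stake is about 5%. Every imbalance figure rests on assumed shares and assumed differences between strata, since the documents give neither.

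**What to change.** Amend section 3.6.2 so that GPCC, which already coordinates the study, releases each assignment by telephone or web only after the consented patient has been registered. Generate the lists in permuted blocks of randomly varying size, with the sizes withheld from recruiters.

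Stratify by index diagnosis (COPD, CHF, both) and also by hospital if the expected numbers keep the strata large enough. Otherwise stratify by one factor and name the other as a covariate in the logistic regression.

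The cost is a call or log-in for each patient, some incomplete blocks, and slightly more predictable sequences within blocks, which varying and undisclosed sizes limit.

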### 3.6.3 Inclusion criteria

- History of confirmed diagnosis of COPD and /or CHF
- Admission to hospital for relapse /worsening symptoms of COPD and/or CHF
- Age:  $\geq 50$
- National registration within the Västra Götaland Region (VGR)
- Owning a phone and current subscription to a telephone service provider

### 3.6.4 Exclusion criteria

Severe hearing impairment that prevents patient from using a telephone or other communication device

Patient has no registered address

Any severe disease with an expected survival  $< 12$  months

Cognitive impairment (SPMSQ score  $> 6$ )

Ongoing documented diagnosis of alcohol or drug abuse

Other disease that can interfere with follow-up (e.g. severe depression, other severe mental illness)

Patient participating in another randomized study

### 3.6.5 Number of patients – Power analysis

To achieve 80 % power with an alpha-error of 0.05 for an increase in the number of patients with improved self-efficacy  $> 5$  units from 20% to 40%, the number of participants in each group (comparison and intervention) needs to comprise 91 patients. We aim to include 110 patients in each group to have some margin for withdrawals/ dropouts

## 3.7 The intervention

### 3.7.1 The patient programme: Contents or ‘Building blocks’ of the intervention

The intervention consists of a communication and on-going dialogues between patients, their informal carers and tele-support nurses. The communication with the patient will be based on the principles of person-centred communication (Listening, open questions, reflective listening and summarising of narrative) (Fors, 2014).

The intervention comprises four main 'building blocks'.

'Building blocks' of the intervention:

- **Coaching, motivation and empowerment** of the patient and informal carer: Patients suffering from a chronic disease often experience anxiety and depression. These may worsen disease symptoms and hamper effective self-management (DeJean, Giacomini, Vanstone, & Brundisini, 2013). Coaching and counselling towards self-management of patients (and their informal caregivers) will be part of the programme.
- **Pedagogical conversations:** Discussing the disease, medical treatment, and its management in daily life as per patient's needs: Patients suffering from COPD and/or CHF do not receive education about their disease that is tailored to their needs, so they often have minimal knowledge about their condition. The program aims to fill knowledge gaps by providing adequate information as per the patient's (and informal care givers') needs and abilities.
- **Monitoring of signs and symptoms** via a smartphone application (Symgo)
- **A personal Health Plan:** A regularly updated record of a mutually agreed health plan based on the patient's illness narrative. The personal Health Plan is a document for tracking care processes, it is maintained and held by the patient. This personal plan will be re-evaluated on a frequent basis, on every appointment with the tele-nurse. The health plan will contain patients' aims and goals for living with and management of their disease.

### 3.7.2 Delivery of the intervention

The delivery of the intervention will commence during the patient's hospital stay. In an initial face-to-face meeting between patient and nurse, the patient's illness narrative will be elicited and the mutually agreed personal Health Plan will be formulated in partnership with the patient. The plan comprises a written record of the patient's personal goals and aims. Aims and goals may relate to

1. Regular physical activity
2. Regular social activity
3. Symptom management
4. Increasing wellbeing
5. Or other personal aims or goals as identified by the patient

As per patient preference, the health plan will be either in electronic or paper format. The patient keeps the Health Plan, yet might give read-only access to other health care providers such as hospitals or primary care centres.

## The Health Plan

- THE Core document for tracking patients' aims and goals in the care relationship
- Based and formulated on the condensed patient narrative
- Will not include medical information included in other patient records
- Mutually agreement of goals and aims between patient and nurse, identification of patient's resources and support needs.
- Also contains: follow-up actions, steps to be taken towards achieving the goals, planning and documentation of care processes in the community: e.g. primary care centre, social welfare centre, appointment times and dates
- Held and maintained by the patient who may give read-only access to care providers (e.g. Hospital, primary care centre)
- Regularly revised and updated during each patient-nurse contact: The nurse will update the plan and share it with the patient for his or her comments.
- May be in paper or electronic format, depending on patient preference

Figure 2: The Health Plan

### **3.7.2.1 During the hospital stay: Initiating the contact**

The nurse will visit the patient to formulate the patient's personal Health Plan in partnership. Based on the initial dialogue with the patient, the nurse will draft the HP and share this draft with the patient for comments and approval. Once approved by the patient, the HP will be uploaded onto an online personal health diary that allows the patient to access the HP. The patient can also grant read-only access to the HP to care providers such as the hospital, outpatient clinics or primary care centres. A copy of the HP will also added to the patient's medical journal as a research note.

### **3.7.2.2 At discharge**

On discharge, the nurse and patient will meet again to revisit the HP and to schedule the first telephone support call. If needed, the patient may also contact the nurse prior to the scheduled telephone support call.

If the PCC health plan is updated, the PCC nurse will send the updated version both to the patients' online health diary as well as the medical journal as a research note.

### **3.7.2.3 At home**

After discharge from hospital, the nurse will contact the patient at mutually agreed intervals to revisit personal goals, to educate, motivate and coach the patient, as well as to discuss symptom management. During each telephone call, the HP will be updated by the nurse and then shared with the patients for comments and approval. New appointment times will be scheduled at each telephone support call. Patients informal carers will be involved.

Supplementary support: The service will be set up in collaboration with representatives from Swedish patient support groups (Riksförbundet HjärtLung), so patients will also be offered access to a network of support initiatives organised by patients. Each patient will be looked after by a 'pool' of two to three nurses to ensure that patients benefit from the wide range of professional experience. If patients are being re-admitted for

worsening condition during the intervention period, the support will continue once they have been discharged from the respective hospital episode.

### 3.7.3 Technical features

During the hospital stay, the patient can familiarize her/himself with the personal support record, which consists of

- The Health Plan
- A personal diary
- An instrument to track trends in signs and symptoms over time (e.g. breathlessness, fatigue)

The patient will receive an individual user name and access to the diary will be password protected. The diary may be accessed via smartphone, tablet or computer. All data will be stored, managed and be made accessible in line with PuL (Personuppgiftslagen) legislation and with Gothenburg University's guidelines on data protection.

## 3.8 Baseline data

**Demographics:** Sex, age (year), education, employment, socio-economics, marital status.

**Characteristics:** Height, weight, waist and hip.

**History:** Smoking, Co- morbidity; Chronic obstructive pulmonary disease, Chronic heart failure, Stroke, Atrial fibrillation/flutter, Diabetes, Hypertension and Cancer.

COPD – number of admission before current indexed admission

### 3.8.1 Assessment

**Self assessment** at baseline and follow-up (3 and 6 months)

Patients

- Health related Quality of Life - EQ-5D (Brooks, 1996; Wittrup-Jensen, Lauridsen, Gudex, & Pedersen, 2009)
- General Self- Efficacy scale (Schwarzer & Jerusalem, 1995),
- Cardiac-Self Efficacy Scale (Fors, Ulin, Cliffordson, Ekman, & Brink, 2014),
- Beliefs about Medicines Questionnaire BMQ, specific (Horne, Weinman, & Hankins, 1999)
- Shortness of Breath in Heart Failure (SOB-HF) (Ekman, Granger, Swedberg, Stenlund, & Boman, 2011)
- COPD Assessment Test (CAT) (GlaxoSmithKline, 2009)
- Fatigue Impact Scale (FIS) (Flensner, Ek, & Soderhamn, 2005)
- Hospital anxiety and depression scale (HADS) (GL Assessments)

Carers:

- Cope Index

## Health Service utilization

- Readmission rates to hospital for worsening COPD and/or CHF
- Visits to vårdcentral/hospital *to be updated*.

### 3.9 Statistical methods and analysis

The statistical analyses will have a significance level of 5 % and, when relevant, 95 % confidence intervals will be reported. Mean values will be compared using t-tests and non-parametric tests will be used for analysis of nominal and ordinal data. Logistic regression will be used to study the co-variation of descriptive variables in relation to the results.

Regarding descriptive statistics, absolute numbers and percentages will be calculated for nominal variables; means and standard deviations will be computed for normally distributed continuous variables; and medians and quartiles will be calculated for non-normally distributed variables.

The primary outcomes in the intervention and control groups will be compared by ....

All analyses will have a significance level of 0,05 %, and 2-sided tests will be used.

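### Mean scores are to be compared by unadjusted t-tests although the baseline score is collected; adjusting for it would give a more precise estimate at almost no cost

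*Protocol*

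**What the plan says.** Protocol section 3.9 sets the method for continuous outcomes in general terms: "Mean values will be compared using t-tests". The same sentence adds that "non-parametric tests will be used for analysis of nominal and ordinal data". The only regression model named is logistic: "Logistic regression will be used to study the co-variation of descriptive variables in relation to the results". No ANCOVA, mixed model or other baseline-adjusted comparison of means appears in the protocol.

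Section 3.4.2 lists "Change in Self-Efficacy" as secondary endpoint (b). Section 3.8.1 has the patient questionnaires, including two self-efficacy scales, completed "at baseline and follow-up (3 and 6 months". The baseline value of each score will therefore be in the database.

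**The concern.** When a score is measured before and after randomisation, its baseline value is usually among the best predictors of its follow-up value. A two-sample t-test either leaves the baseline out (comparison of 6-month scores) or subtracts it in full (comparison of change). Neither is the best use of it unless the correlation happens to be 0 or 1. The logistic regression in section 3.9 does not fill the gap, because it cannot produce an adjusted difference in mean scores and its stated purpose is to study descriptive variables.

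Two things are at stake for secondary endpoint (b). The confidence interval will be wider than it needs to be. In addition, if the arms differ at baseline by chance, part of that difference carries into the estimated effect. Section 3.6.2 describes 1:1 allocation from computer-generated lists and mentions no stratification, so the design as written does nothing specific to limit such a difference.

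**Working it through.** **The plan's own figure.** Section 3.6.5 gives the sample size: "To achieve 80 % power with an alpha-error of 0.05", "from 20% to 40%, the number of participants in each group (comparison and intervention) needs to comprise 91 patients". Section 3.9 states that "2-sided tests will be used". For two proportions, two-sided 0.05 and 80% power:

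- Without continuity correction: n = [1.960·√(2·0.30·0.70) + 0.842·√(0.16 + 0.24)]² / 0.20² ≈ 81.2, so 82 per group.
- With continuity correction: n = (81.2/4)·[1 + √(1 + 4/(81.2·0.20))]² ≈ 90.9, so 91 per group.

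The stated 91 is reproduced exactly with the continuity correction. It concerns a binary outcome and does not depend on how mean scores are analysed. It is used below only as an illustrative number of scored patients per group.

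**Variance of the estimated effect.** Let s be the SD of the score, assumed equal at baseline and 6 months, and rho the correlation between the two. Per patient:

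- t-test on the 6-month score: s²
- t-test on change: 2(1 − rho)s²
- ANCOVA: (1 − rho²)s²

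The ratios are (1 − rho²)/[2(1 − rho)] = (1 + rho)/2 for ANCOVA against change, and 1 − rho² for ANCOVA against the 6-month score. The protocol gives no rho, so a range is shown.

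| rho (assumed) | 6-month t-test | Change t-test | ANCOVA | ANCOVA / change | ANCOVA / 6-month |
|---|---|---|---|---|---|
| 0.3 | 1 | 1.40 | 0.91 | 0.65 | 0.91 |
| 0.4 | 1 | 1.20 | 0.84 | 0.70 | 0.84 |
| 0.5 | 1 | 1.00 | 0.75 | 0.75 | 0.75 |
| 0.7 | 1 | 0.60 | 0.51 | 0.85 | 0.51 |
| 0.8 | 1 | 0.40 | 0.36 | 0.90 | 0.36 |

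For rho 0.4 to 0.7:

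- Against change, √0.70 = 0.84 and √0.85 = 0.92, so intervals are 16% to 8% narrower. Since 1/0.70 = 1.43 and 1/0.85 = 1.18, that is worth 43% to 18% more patients.
- Against the 6-month score, √0.84 = 0.92 and √0.51 = 0.71, so intervals are 8% to 29% narrower.

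**The direction does not rest on equal SDs.** With baseline SD s0 and follow-up SD s1, the variance of change is s0² + s1² − 2·rho·s0·s1 = (s0 − rho·s1)² + (1 − rho²)s1². This is never below the ANCOVA variance (1 − rho²)s1². Only the size of the gain depends on the assumption.

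**Power, for illustration.** With 91 per group, a t-test on the 6-month score has 80% power at a true difference of (1.960 + 0.842)·√(2/91) = 0.415 SD. At that difference:

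| rho | Change t-test | ANCOVA |
|---|---|---|
| 0.3 | 65.8% | 83.6% |
| 0.5 | 80.0% | 89.9% |
| 0.7 | 95.1% | 97.5% |

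**Chance imbalance.** With 91 per group, the baseline difference between arms has standard error √(2/91) = 0.148 SD, so its 95% range is ±1.96·0.148 = ±0.29 SD. If the difference is +0.29 SD, the expected shift in the estimate is rho·0.29 for the 6-month t-test and −(1 − rho)·0.29 for the change t-test:

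| rho | 6-month t-test | Change t-test |
|---|---|---|
| 0.3 | +0.087 SD | −0.203 SD |
| 0.5 | +0.145 SD | −0.145 SD |
| 0.7 | +0.203 SD | −0.087 SD |

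ANCOVA removes this shift in expectation.

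**The case against.** The strongest reply is that nothing here is wrong. Under 1:1 randomisation a two-sample t-test on final or change scores is unbiased over repeated randomisations and holds its type I error. Covariate adjustment of a secondary score is often left to an SAP, and section 3.9 is a general and visibly unfinished paragraph. The first part stands in full: the loss is one of precision, together with bias conditional on an observed baseline imbalance. A reader might infer that the planned test is invalid, and the protocol does not support that. On the second part, the protocol does not leave the method open. It names the t-test, and a reader would take that as the plan.

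Four further limits stand.

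- **Scope.** A reader might infer that every questionnaire will be t-tested. Section 3.9 does not assign scales to tests, and scores treated as ordinal would go to non-parametric tests, which are also unadjusted as written. Of the scores, only change in self-efficacy is listed as a secondary endpoint in section 3.4.2.
- **Uncorrected imbalance.** It would be too strong to say that t-tests simply leave imbalance uncorrected. That is true of the 6-month comparison; a change score subtracts too much.
- **Hospital admission.** Because patients are enrolled in hospital, a reader might infer that regression to the mean distorts the comparison. Section 3.8.1 does not say when baseline is taken. Recovery after admission would in any case affect both randomised arms alike and cancel in the difference. Only chance imbalance between arms matters, as in any trial.
- **Size.** The gain rests on an assumed rho and on which t-test is meant. At rho 0.3 the variance falls by 35% against change but only 9% against the 6-month score.

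**Conclusion.** The point holds as a free improvement, not as an error. For secondary endpoint (b), and any other scale score compared by means, the stated t-test uses the available baseline less well than ANCOVA. Assuming equal SDs and rho between 0.4 and 0.7, ANCOVA has 0.70 to 0.85 of the variance of the change-score t-test and 0.84 to 0.51 of that of the 6-month t-test. The direction holds for any rho, apart from the negligible cost of estimating one slope; the size depends on a rho that the protocol does not give.

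A reader might extend this to the main result or to the sample size. The protocol does not support that: the primary outcome in section 3.4.1 is a composite classification, the test for it is left blank in section 3.9, and the 91 per group is for a binary comparison.

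**What to change.** In section 3.9, replace the t-test for secondary endpoint (b), and for any other scale score compared by means, with ANCOVA: 6-month score as outcome, treatment group and the baseline score of the same scale as covariates, reporting the adjusted mean difference with its 95% CI. With the baseline score as covariate, the estimated effect is the same whether the outcome is the 6-month score or the change, so endpoint (b) need not be redefined.

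A mixed model on the 3- and 6-month scores with baseline as covariate is a reasonable alternative. It is not equivalent: with incomplete follow-up it uses different patients and rests on different missing-data assumptions. One of the two should be chosen before outcome data are seen by arm, which also prevents a later choice between change, final and adjusted scores.

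The cost is one sentence in a section that has to be completed anyway. No extra data, visits or patients are needed. If an SAP already specifies baseline adjustment, section 3.9 only has to be aligned with it.

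### The sentence naming the primary comparison is unfinished, and the three-level primary outcome is not matched to the two-proportion sizing, so the stated 80 % power is tied to only one of the tests that the protocol allows

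*Protocol*

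**What the plan says.** Four parts of the protocol bear on the primary test.

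- **Section 3.4.1** sorts each patient into one of three levels. Improved needs a gain of more than 5 units at 6 months and no re-admission. Worsened is death, re-admission within 6 months, or a loss of more than 5 units. Unchanged is the remainder: "Self-efficacy has neither improved or deteriorated".
- **Section 3.6.5** sizes the trial on a single proportion: "To achieve 80 % power with an alpha-error of 0.05 for an increase in the number of patients with improved self-efficacy" by more than 5 units, "from 20% to 40%, the number of participants in each group (comparison and intervention) needs to comprise 91 patients". The recruitment target adds a margin: "We aim to include 110 patients in each group to have some margin for withdrawals/ dropouts". No expected rate is given for Worsened or Unchanged.
- **Section 3.9** gives a general rule, "non-parametric tests will be used for analysis of nominal and ordinal data", without naming a test. Logistic regression appears there only for relating descriptive variables to the results.
- **Section 3.9** then begins the sentence that should fix the primary test, "The primary outcomes in the intervention and control groups will be compared by", and ends it in dots. The text neither fills the gap nor refers it to another document.

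**The concern.** The outcome definition, the sample size and the analysis section should describe one comparison. Here the first has three levels, the second has two, and the third is blank. A reader who fills the blank from the rest of the protocol can reach at least three tests: Improved vs not (from 3.6.5), a 2-df chi-square on three categories (nominal data under 3.9), or a rank test on three ordered levels (ordinal data under 3.9). These answer different questions and have different power at the same sample size.

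Two things are at stake. The power stated in 3.6.5 may not be that of the test that is run. And if the choice were made once the data are in, the nominal 5 % would no longer be the false-positive rate.

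**Working it through.** **1. Reproduce the 91.** Inputs from 3.6.5, 3.6.2 and 3.9: p1 = 0.20, p2 = 0.40, mean 0.30, power 80 %, alpha 0.05 two-sided, allocation 1:1.

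n = [1.96 × √(2 × 0.3 × 0.7) + 0.842 × √(0.2 × 0.8 + 0.4 × 0.6)]² / 0.2² = (1.270 + 0.532)² / 0.04 = 81.2, so 82 per group.

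With continuity correction: n' = (81.2 / 4) × [1 + √(1 + 4 / (81.2 × 0.2))]² = 90.9, so **91**, the protocol's figure.

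A one-sided version gives 64, or 74 with correction. The sizing is therefore a two-sided binary comparison of Improved vs not. At 91 per group its power is 80 % with continuity correction and about 84 % without.

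**2. Power of a rank test on three levels.** Improved is held at 20 % vs 40 %. The Worsened rates are assumptions, because the protocol gives none. With levels ordered Worsened < Unchanged < Improved, let θ be the probability that an intervention patient does better than a control patient, ties counting half. Power is approximately Φ[(θ − 0.5 − 1.96 × SE0) / SE1]. SE0 is the tie-corrected standard error of the estimate of θ under the null, and SE1 the one under the alternative.

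Example, Worsened 40 % in both arms: control (0.4, 0.4, 0.2), intervention (0.4, 0.2, 0.4).
- θ = 0.4 × 0.2 + 0.2 × (0.4 + 0.2) + 0.4 × (0.8 + 0.1) = 0.56.
- Pooled shares are (0.4, 0.3, 0.3), with sum of cubes 0.118. SE0 = √[(1 − 0.118) / 12 × 2 / 91] = 0.0402, and SE1 = 0.0404.
- Power = Φ[(0.06 − 0.0788) / 0.0404] = Φ(−0.46) = 32 %.

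The same calculation, checked by 40,000 simulated trials per scenario, at 91 per group and two-sided 5 %:

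| Worsened, control → intervention (assumed) | Rank test | 2-df chi-square (simulated) |
|---|---|---|
| 30 → 30 % | 41-42 % | 85 % |
| 40 → 40 % | 32 % | 90 % |
| 50 → 50 % | 25 % | 96 % |
| 30 → 20 % | 80 % | 78 % |
| 40 → 30 % | 70 % | 76 % |
| 50 → 40 % | 62 % | 78 % |
| 20 → 10 % | 89 % | 82 % |
| 40 → 20 % | 94 % | 90 % |

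The rank test reaches 80 % once Worsened falls by about 7 points from 20 %, 10.5 points from 30 % or 13 points from 40 %. With the full 110 per group and equal Worsened rates of 30, 40 and 50 %, it has about 48, 38 and 29 %.

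**3. Type I error if the test is picked afterwards.** Simulated null: Improved 20 % in both arms, Worsened 30, 40 or 50 % in both arms (assumed), 91 per group, 100,000 trials each. Each test alone rejects in about 5 %. The chance that at least one rejects is:
- Improved vs not, or the rank test: about 8 %;
- adding the 2-df chi-square: 9-10 %;
- adding Worsened vs not: 10-11 %.

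**4. The sized event and the defined event.** Section 3.6.5 speaks only of a gain of more than 5 units, whereas Improved in 3.4.1 also requires no re-admission. Even the binary reading therefore does not show that the 20 % and 40 % refer to the primary outcome as defined.

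**The case against.** A reader might infer that 3.9 dictates a rank test and so contradicts the sizing. It does not. The rule covers nominal as well as ordinal data and names no test. A chi-square test is non-parametric and fits it, including on Improved vs not. Section 3.4.1 does not say that the levels will be ranked.

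A reader might also infer that a rank test necessarily dilutes the effect, or that its power has a fixed range below 80 %. Neither follows. Section 3.3 expects fewer hospital re-admissions, and re-admission is part of Worsened. On the trial's own hypothesis Worsened should fall, and if it falls enough the rank test beats the planned power. Across other assumed rates, including a rise in Worsened, its power runs from about 12 % (30 → 40 %) to over 97 % (30 → 10 %). Losses should be judged against the design's 80 %, not the 84 % of the uncorrected test; on that basis the 30 → 20 % case loses nothing.

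Finally, a statistical analysis plan may exist and may fix the test before the data are seen. The protocol therefore does not show that type I error is in fact inflated; the 8-11 % is what an after-the-fact choice would cost.

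All of this stands. It leaves untouched that the sentence is unfinished in the current text, that the outcome has three levels while the sizing has two, and that the stated power was derived for only one admissible test.

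**Conclusion.** The point holds as a gap and a mismatch. The protocol starts to state its primary comparison and does not finish, and its outcome definition and its sizing point to different comparisons. The 80 % was calculated only for Improved vs not. For the other admissible tests the power cannot be known from the document: for a rank test it could be a third of the planned value or well above it, depending on Worsened rates that are not given. The figure of 91 per group is itself correct for the comparison it was computed for. The power figures for the rank and 2-df tests rest on assumed Worsened rates with Improved fixed at 20 % vs 40 %; the type I figures rest on assumed null rates and on a data-dependent choice.

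**What to change.** Complete the sentence in 3.9 along these lines: the primary comparison is the proportion Improved as defined in 3.4.1 (including no re-admission) vs Unchanged or Worsened at 6 months, in all randomised patients as randomised, two-sided 5 %, by logistic regression adjusted for the baseline score of the self-efficacy scale used for the outcome; the three-level distribution is supportive.

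Three matching edits are needed:
- Name the scale. Section 3.8.1 lists two, a general and a cardiac one.
- State in 3.6.5 that the 20 % and 40 % refer to Improved as defined in 3.4.1, or revise them.
- Remove the 0,05 % in 3.9, which conflicts with the 5 % given earlier in that section and with the 0.05 in 3.6.5.

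If an ordinal test is preferred, name it and restate the power from stated rates for all three levels.

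The cost is a few lines of text and no new data, since self-efficacy is already collected at baseline. The adjusted regression is not literally the two-proportion test that was sized, so the unadjusted proportions should be reported beside it. The real downside is that differences between Worsened and Unchanged do not count in the primary test. The secondary endpoints cover these only partly: re-admissions and change in self-efficacy are listed in 3.4.2, death is not.
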